### **11.5. Decision points**

No interim analysis is planned.

### **11.6. Stopping rules**

The TSDMEC will formally recommend early termination if needed based on review of the AEs and SAEs. To facilitate TSDMEC decision making, the following recommendation for a pre-defined cut-off will apply. If no SAEs have occurred in the control group and the lower bound of the 95% confidence interval for SAEs is at least 30% in the intervention group based on a one-sample test for binomial proportion (Wilson score), the trial will stop.

### **11.7. The Level of Statistical Significance**

The level of statistical significance will be set at  $p < 0.05$ . There will be no adjustment for multiple testing. The 95% confidence intervals will be presented but regarded nominal and descriptive.

### **11.8. Procedure for Accounting for Missing, Unused, and Spurious Data.**

Missing data will be imputed using appropriate methodology as detailed in the SAP.

### **11.9. Procedures for Reporting any Deviation(s) from the Original Statistical Plan**

Deviations from the original SAP will be reported and justified at publication following the CONSORT guidelines.

### 11.10. Progression criteria to a full trial

|   | Criterion Decision                                                                                                                | Green Progress                                                             | Amber Progress with changes | Red Stop |
|---|-----------------------------------------------------------------------------------------------------------------------------------|----------------------------------------------------------------------------|-----------------------------|----------|
| 1 | Recruitment
(Proportion of eligible patients that have been randomised)                                                        | ≥25%                                                                       | 11-24%                      | ≤10%     |
| 2 | Adherence
(Proportion of participants in the intervention group who commenced the programme with ≥10% weight loss at 16 weeks) | ≥60%                                                                       | 46-59%                      | ≤45%     |
| 3 | Retention
(Proportion of randomised participants completing a 24-week follow-up visit)                                         | ≥85%                                                                       | 66-84%                      | ≤65%     |
| 4 | Safety profile                                                                                                                    | Based on adverse and serious adverse reactions. Adjudicated by the TSDMEC. |                             |          |

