#### **9.5. Blinding and code-breaking**

It is impossible to blind the participants and clinicians to the treatment due to the nature of the intervention. Therefore, procedures for breaking the allocation code are not applicable. The independent assessor of the MRI/MRE scans (for the assessment of the primary outcome) will be blinded to allocation.

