### **Acute liver dysfunction**

Due to the challenge of recognizing and diagnosing acute liver dysfunction in subjects with pre-existing liver dysfunction, the TSDMEC will review potential cases of acute liver dysfunction and classify them as:

- Acute liver dysfunction attributable to the intervention could be excluded (there is a clear alternative explanation)
- Acute liver dysfunction attributable to the intervention could not be excluded (there is no clear alternative explanation)
- Indeterminate due to insufficient data.

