### **10.2. Reporting Procedures for Serious Adverse Events**

A serious adverse event (SAE) occurring to a participant will be reported to the REC that gave a favourable opinion of the study where in the opinion of the Chief Investigator the event was 'related' (resulted from administration of any of the research procedures) and 'unexpected' in relation to those procedures. Reports of related and unexpected SAEs will be submitted within 15 working days of the Chief Investigator becoming aware of the event, using the HRA report of serious adverse event form (see HRA website).

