### **11.4. Analysis populations**

All randomised participants be included in the main analysis. A per protocol analysis will include the sub-sample of intervention participants who achieved ≥10.0% weight loss at 4 months. The adverse event analysis will include the participants commencing the intervention.

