### 13.3.2 Trial Steering, Data Monitoring, and Ethics Committee (TSDMEC)

As this is an unblinded trial, the Trial Steering Committee and the Data Monitoring and Ethics Committee will be combined. The TSDMEC of 3 independent members [chair (hepatologist), academic with expertise in clinical trials, clinician] will review and meet online to approve the protocol and meet thereafter every 6 months or following completion of the 4-week follow-up of 8 randomised participants (whichever is earlier) to review data quality and monitor ethics and safety based on unblinded data and advise the TMG. The TSDMEC may meet more frequently and request to review specific analyses (e.g. comparing rates of AEs by trial group or other subgroup) at their discretion and as needed. They will review an extra safety profile report between the scheduled meetings of biochemistry and relevant data of participants discontinuing the intervention or being on enhanced observation. They will review SAEs as they occur. They will formally recommend at the end of each meeting whether the trial should continue with no changes, continue with protocol modifications, or be stopped. Its role, constitution, and composition will follow NIHR guidelines.

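### The safety progression criterion rests on open-label attribution of undefined 'reactions' and leaves out the randomised comparison and the co-primary biochemistry

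*Protocol*

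**What the plan says.** Section 11.10 lists four progression criteria. Recruitment, adherence and retention have numerical green, amber and red bands. The fourth, the safety profile, has one entry across all bands: "Based on adverse and serious adverse reactions. Adjudicated by the TSDMEC". The protocol does not define an adverse reaction. The nearest text is in section 10.2, where, for ethics committee reporting only, 'related' means "resulted from administration of any of the research procedures".

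The adjudicating committee (TSDMEC) meets "to review data quality and monitor ethics and safety based on unblinded data and advise the TMG" (section 13.3.2). On participants and clinicians, section 9.5 says: "It is impossible to blind the participants and clinicians to the treatment due to the nature of the intervention".

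Section 11.4 fixes the safety analysis set: "The adverse event analysis will include the participants commencing the intervention". Controls are not named there.

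For acute liver dysfunction, section 10 has the committee sort cases by whether the intervention can be ruled out as the cause. One of the three classes is "Acute liver dysfunction attributable to the intervention could not be excluded (there is no clear alternative explanation").

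The stopping guideline in section 11.6 is framed differently. It refers to SAEs with no attribution step and looks at both arms: "If no SAEs have occurred in the control group and the lower bound of the 95% confidence interval for SAEs is at least 30" per cent in the intervention group, the trial stops.

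**The concern.** Safety signals are the first co-primary objective (section 6), and the trial was designed because rapid weight loss might worsen a cirrhotic liver (section 5). Decompensation, reaching the MELD threshold for transplantation and hepatocellular carcinoma are pre-specified SAEs (section 10.1). All of these also occur in the natural course of the disease. A single patient's record will often not show whether the diet caused such an event, and section 10 itself says acute liver dysfunction is hard to recognise in people whose liver function is already impaired. The control arm is there to show how often such events happen without the diet.

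A criterion confined to reactions replaces that comparison with a causality opinion formed in knowledge of the arm. The error can go either way. Background events may be charged to the diet, or a real excess may be put down to the disease. The decision at stake is whether a full trial goes ahead.

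**Working it through.** The protocol gives no figure for this criterion, so there is none to reproduce. The check compares the relevant sections and then illustrates the effect on assumed rates.

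**1. What enters the criterion, and what is available.**

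- Events: 11.10 uses reactions. Sections 10, 10.1 and 11.6 use adverse events and SAEs, without an attribution step.
- Arms: 11.10 names none, and 11.4 names only those starting the intervention. Yet section 10 opens the safety window for controls at randomisation, and section 6 lists adverse events as an outcome at weeks 0, 2, 4, 16 and 24. The control data will therefore exist.
- Biochemistry: section 6 makes severe change in ALT, AST or total bilirubin a co-primary outcome. It needs no causality opinion. Criterion 4 does not mention it.
- Masking: none for participants, clinicians or the committee. Section 9.5 blinds only the reader of the scans.
- Between-arm rates: section 13.3.2 gives these as an example of what the committee may request at its discretion. They are not part of the criterion.

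**2. How far attribution alone can move the result.** Inputs: 16 intervention and 8 control participants (section 11.3). Assumptions, since the protocol gives no background rate: each participant has the same risk p of at least one event in either arm, participants are independent, and a share q of affected diet participants is judged to have had a reaction.

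Expected reactions = 16 × p × q. Chance of at least one = 1 − (1 − pq)^16.

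| p | q = 25% | q = 50% | q = 100% |
|---|---|---|---|
| 10% | 0.4 (33%) | 0.8 (56%) | 1.6 (81%) |
| 20% | 0.8 (56%) | 1.6 (81%) | 3.2 (97%) |
| 30% | 1.2 (71%) | 2.4 (93%) | 4.8 (99.7%) |

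Example for p = 10%, q = 50%: 16 × 0.10 × 0.50 = 0.8, and 1 − 0.95^16 = 0.56.

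Within each row there is no true effect, and the expected number changes fourfold with q alone.

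**3. The same reaction figure can come from different truths.** Let the control risk be 10%, so 8 × 0.10 = 0.8 control participants are expected to have an event.

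- No effect: diet risk 10%, all attributed. Reactions 16 × 0.10 × 1 = 1.6. All events by arm: 1.6 v 0.8, the 2:1 expected from the allocation.
- Doubled risk: diet risk 20%, half attributed. Reactions 16 × 0.20 × 0.5 = 1.6. All events by arm: 3.2 v 0.8.

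The reaction figure is identical. Only the tabulation by arm differs.

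**4. What the comparison can and cannot give.** For 0 events in 8 controls the Wilson 95% upper limit is z²/(n + z²) = 3.84/(8 + 3.84) = 32.4%. With 0/8 in controls, a two-sided Fisher test first falls below 0.05 at 8/16 diet participants (p = 0.022; 7/16 gives 0.054). The contrast is coarse and can only be descriptive.

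**The case against.** The best defence is that expert review is reasonable in a 24-person feasibility trial and that the committee is well placed to do it. Several parts of this stand.

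- The committee is independent, sees both arms, reviews SAEs as they occur and can ask for rates by group. A reader might infer that the comparator is withheld from it. That is not so; the comparator is missing only from the criterion.
- A reader might also infer that reactions are counted and that the control count is zero by construction. Criterion 4 states no count or threshold. In the section 10.2 sense of relatedness, a control could have an event caused by a study procedure such as the scan or the performance test. The zero holds only for reactions to the diet.
- The liver dysfunction classification leans against the diet: without a clear alternative explanation, attribution stays open. That makes it less likely that harm is readily dismissed.
- Some biochemistry reaches the committee. Section 10 requires abnormalities that trigger enhanced observation or discontinuation to be recorded as adverse events, and section 13.3.2 provides a between-meeting report on the participants concerned. Neither is a summary of the co-primary criteria by arm.
- Sections 11.6 and 11.10 serve different decisions, so their different event definitions are not a contradiction.
- Section 11.4 may have been meant only to drop intervention participants who never start. As written, it leaves the controls out.

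None of these points puts the randomised comparison into the stated criterion.

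**Conclusion.** The point holds as a matter of what the protocol states. Followed as written, the safety go/no-go rests on an undefined and normally attribution-based category, judged with knowledge of the arm. The control events and the objective co-primary biochemistry are not part of it.

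The size is illustrative. On assumed risks of 10% to 30% that are equal in both arms, the expected number of reactions in 16 varies fourfold as the attributed share goes from 25% to 100%. This depends on the assumed risks and shares, on independence between participants, and on reading 'reaction' in its usual sense. No probability of a wrong decision follows, because the criterion has no boundary. Nor would the randomised contrast settle causality, as a reader might hope: with 8 controls it informs the committee's judgement and cannot replace it.

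This is a cheap improvement to the decision rule and does not invalidate the trial.

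**What to change.** Reword criterion 4 in section 11.10 to: *All adverse events, serious adverse events and co-primary biochemical criteria, summarised by randomised arm and reviewed by the TSDMEC, with causality assessment as supporting information.* Amend section 11.4 so that the adverse event analysis includes the control group.

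The cost is one table row and one sentence. No new data, visits or committee members are needed. The downside is that unrelated events enter the summary and the control rate is imprecise, so the comparison should be labelled descriptive.

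Arm-masked adjudication is not part of this request. It would need someone to prepare redacted case summaries, and the enhanced observation history in section 10 records adherence to the diet, which would make the masking fragile.

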## 12. DATA MANAGEMENT

The plan for the data management of the study are outlined below. There is not a separate Data Management document in use for the study.

### 12.1. Source Data

Source documents are where data are first recorded, and from which participants' CRF data are obtained. These include, but are not limited to, hospital records (from which medical history and previous and concurrent medication may be summarised into the CRF), clinical and office charts, laboratory and pharmacy records, radiographs, questionnaires, and correspondence.

CRF entries will be considered source data if the CRF is the site of the original recording (e.g. there is no other written or electronic record of data). All documents will be stored safely in confidential conditions. On all study-specific documents, other than the signed consent, the participant will be referred to by the study participant number/code, not by name.

### 12.2. Access to Data

Direct access will be granted to authorised representatives from the Sponsor and host institution for monitoring and/or audit of the study to ensure compliance with regulations.

The MRI scans will be processed by a third-party, Perspectum Diagnostics, using their software. See sections 12.3 and 17.3 for further details. The MRE scans will be processed within the University of Oxford.

Following participants' consent, Oviva will be granted access to the participants' name, home address, contact details, demographic details, and relevant medical information (such as weight, height, blood pressure, blood tests, medical history, and medication), so that the intervention sessions with the dietitians can take place. See section 12.3 for further details. Contractual arrangements will follow section 17.3.

Nestle Health Science will have no access to the study data.

De-identified data obtained as part of this study may be used in future research, here or abroad, and may involve commercial organisations.

### **12.3. Data Recording and Record Keeping**

This study will be run using the Primary Care Clinical Trials Unit (CTU) standard operating procedures (SOPs) for guidance.

All trial data will be entered on to paper CRFs. Data will be transferred to the statistical software for analysis and validation checks will be performed (e.g., range checks). The participants will be identified by a unique trial specific number and/or code in any database. The name and any other identifying detail will NOT be included in any trial data electronic file.

The Oviva electronic medical record and the Oviva app are a single technology platform called Oviva Coaching Suite which is compliant with the NHS Digital Data Security and Protection Toolkit. Oviva will retain the participants' data for up to 8 years in line with the NHS Digital Guidance. Oviva will transfer the personal information for secure storage to Switzerland where the required information security standards are being followed. The Oviva-related data management will be in line with the University's Information Security and Data Protection Impact Assessment.

We will only share the following de-identified research data with Perspectum Diagnostics: MRI/MRE scan, age, sex, weight, height, blood test results, and ultrasound results. We will not share any personally identifiable information. Perspectum Diagnostics will retain the data for a maximum of 5 years and may utilise them for future internal research projects in line with the existing Collaboration Agreement with the University of Oxford. Further details of the data sharing between the two parties and relevant data analysis are pre-specified in the Collaboration Agreement.

We will store the de-identified research data (e.g. lab results, questionnaire data) indefinitely and any research documents with personal information (i.e., consent forms) for 3 years securely at the University of Oxford after the end of the study. Hard copies of personal data will be stored in a locked cupboard in a room with limited access at the University of Oxford.

The research and clinical teams will use participant contact details to contact individuals about the research study and make sure that relevant information about the study is recorded for participant care, and to oversee the quality of the study. We will keep identifiable information about participants (i.e., contact details) from this study separate from the research data and for up to 1 year after the study has finished, so that we can inform participants of the results of the study. We will only keep bank details of each participant who provide them for reimbursement of expenses for 7 years after study completion as per University policy.

Prior to database lock, a dataset review will be undertaken by the CI to ensure all queries have been resolved and the dataset is complete.

The Data Management will be compliant with the relevant Sponsor organisation's policy.

#### **12.4. Transfer of MRI Data to Perspectum Diagnostics, UK**

Perspectum Diagnostics provides a dedicated, secure cloud-based portal called quantitative analysis services (QAS) for data and study management (ISO 270001, 21CFR11). This cloud-based image analysis system is hosted in the United States. The portal provides a complete end-to-end solution for anonymised imaging data upload, archiving, monitoring and return as well as troubleshooting queries and automated data alerts. There will be no identifiable information uploaded via this portal. All MRI data will already be de-identified at the time of image acquisition. Participants will be identified in the Perspectum Diagnostic portal by only a second participant ID number. Specifically, a second participant ID unique to the baseline or 24-week scan will be generated which will consist of a random number between 0 and 300, which will be different from the original study ID number, and will be linked with the original study ID. The key between the two study ID numbers will be held securely at the University of Oxford by the CI. At the end of the study, this key which links the two study IDs will be securely destroyed. This process serves two purposes: it does not allow the scan to be identified as baseline or follow-up scan on the system enhancing the blinding process and aims to minimise the risk that the data held by Perspectum Diagnostics can be linked back to the rest of the data held by the University.

Linked-anonymised image DICOM files will be exported securely (encrypted and password protected) using the portal to Perspectum Diagnostics. Data protection would be our paramount importance. Data will not leave the OCMR system until all patient identifiable details are removed. Although data is de-identified, it will still be treated with the same level of security as containing patient details. The de-identified images will be analysed at a dedicated workstation at OCMR. There is a research collaboration agreement between University of Oxford and Perspectum Diagnostics dated 4th September 2014. De-identified data that has been sent to Perspectum Diagnostics may be used for their internal research and development purposes. It will be governed by the amendments made to section 11 of the existing research collaborative agreement between University of Oxford and Perspectum Diagnostics. Hard copy of MRI data files will be stored securely at the study site (OCMR).

### **13. QUALITY ASSURANCE PROCEDURES**

The study may be monitored, or audited in accordance with the current approved protocol, GCP, relevant regulations and standard operating procedures.

#### **13.1. Risk assessment**

A risk assessment and monitoring plan will be prepared before the study opens and will be reviewed as necessary over the course of the study to reflect significant changes to the protocol or outcomes of monitoring activities.

#### **13.2. Study monitoring**

Regular monitoring will be performed according to the current PC-CTU procedures by the study team. Data will be evaluated for compliance with the protocol and accuracy in relation to source documents. Following written SOPs, the monitors will verify that the clinical study is conducted and data are generated, documented and reported in compliance with the protocol, GCP and the applicable regulatory requirements. The procedure outlined in 13.3.2 will be followed for the data that require expert analysis and/or interpretation.

#### **13.3. Study Committees**

##### **13.3.1 Study Management Group**

The study management group will comprise of all named investigators and the trial manager and it will be responsible for the day-to-day running of the trial. The trial manager will update via email the group monthly on trial progress. The group will meet quarterly to evaluate progress and the frequency of the meetings will be adjusted depending on progress.

### 13.3.2 Trial Steering, Data Monitoring, and Ethics Committee (TSDMEC)

As this is an unblinded trial, the Trial Steering Committee and the Data Monitoring and Ethics Committee will be combined. The TSDMEC of 3 independent members [chair (hepatologist), academic with expertise in clinical trials, clinician] will review and meet online to approve the protocol and meet thereafter every 6 months or following completion of the 4-week follow-up of 8 randomised participants (whichever is earlier) to review data quality and monitor ethics and safety based on unblinded data and advise the TMG. The TSDMEC may meet more frequently and request to review specific analyses (e.g. comparing rates of AEs by trial group or other subgroup) at their discretion and as needed. They will review an extra safety profile report between the scheduled meetings of biochemistry and relevant data of participants discontinuing the intervention or being on enhanced observation. They will review SAEs as they occur. They will formally recommend at the end of each meeting whether the trial should continue with no changes, continue with protocol modifications, or be stopped. Its role, constitution, and composition will follow NIHR guidelines.

